The control group will follow the institution’s school activities defined on the school schedule. The only moments of contact with study staff will be during evaluation, pre-, post and following intervention, to assure a proper control condition, in accordance to our research question about intervention works (Holmes et al., 2018). Considering this, further control will be needed for the following factors: contact with research team limited only to evaluation periods to avoid confusing factors such as attention, warmth, or human relationships. In the evaluation stages, the guardians will answer questionnaires and scales to assess sociodemographic and health data, sleep habits and sleep pattern of their child. The children themselves will answer: a scale to assess sleepiness levels, a questionnaire to evaluate the serious game and the game itself, will characterize their bedroom and the activities they perform before sleep. Also, teachers will be informed only essential information about the study and will be instructed to not use the knowledge acquired about sleep in class during the period of the research.

After completion of the intervention, the last two steps, post intervention evaluation and follow-up evaluation, will be conducted after 4 weeks. In these stages sleep habits and sleep patterns will be re-evaluated by the parents. Additional encounters 1 week after each evaluation will be provided to clarify any doubts about filling in the sleep diary and/or use of actiwatch. During these steps the children will be required to answer the Pictorial Sleepiness Scale of Maldonado and to characterize their bedroom and any activities that they perform before sleep at night (**Figure 2**). Thus, there will be three meetings with parents/guardians during evaluation steps, with three more other encounters to elucidate any doubt about assessments. Missing data will result in individuals being excluded without outcome.

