### Intergroup and Intragroups Analysis

Once confirmed that the groups did not present significative differences, the comparison procedure will be conducted. Variables included in sleep patterns (sleep latency, sleep efficiency, sleep and waking up times, total sleep time), sleep hygiene and sleep problems will be considered dependent variables and will be compared between experimental and control groups, during the three points in time where they will be evaluated, using independent student’s *t*-test and chi-square (χ^2^) with odds ratio and dimension of association (Phi and Cramer’s V), depending on the nature of the data. It will allow us to identify if the intervention with the serious game yielded improvements in objective sleep measures and sleep hygiene.

To evaluate possible improvements intragroup, comparisons will be conducted using: ANOVA (F) for repeated measures with Bonferroni’s post test and Q Chochran test. For all numeric variables percentage will be calculated with delta differences (post-test score minus the pre-test score) and percentage’s change [(post-test score) minus (pre-test score) divided by (pre-test score) multiplied by 100]. These measures will allow us to evaluate the intervention’s immediate effects and the maintenance of this effect after 4 weeks.

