### Evaluation of Serious Game “Perfect Bedroom: Learn to Sleep Well”

The statistical analysis will involve analyzing the responses from the evaluation questionnaire and strategies developed by the researchers (“Set up your bedroom” and “Mapping activities before bedtime”). For the questionnaire descriptive analyze and exploration of frequency will be conducted with crosstabs command. It will allow us to characterize the children’s perception of the game in the following aspects: (a) user’s satisfaction and user’s experience; (b) understandability; and (c) enjoyment. These indicators will be collected in a typical Likert scale with a five-point ordinal scale that represents five conditions in binary data (I did not like play = 1; I did like play = 2). In addition, the software package Iramuteq will be used for the qualitative analyze of the open question “How it was to play the game Perfect Bedroom: learn to sleep well?”).

The final point of the evaluation, learning outcomes, will be evaluated with inter and intragroup analysis of the strategies cited below. The activity of mapping bedroom responses will be categorized in binary data (object absent in bedroom = 1; object present in bedroom = 2) and the total of inappropriate and suitable objects present in the bedroom will be counted. Attribution in each group will occur according to previous studies indicating the negative effect of electronic devices in children’s room (Cain and Gradisar, 2010; Cespedes et al., 2014). The same will be for the analysis of the strategy for “mapping activities before bedtime.”

Inferential tests to intragroup and intergroup will be carried out in binary and numeric data, respectively, ANOVA (F) for repeated measures with Bonferroni’s post test and Q Chochran test to intragroup; and independent student’s *t*-test (*t*) or Chi-square test to intergroup analysis.

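### Percent change from baseline is prescribed for every numeric variable, including sleep and wake-up times, where its size and sign depend on how clock time is coded

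*Protocol article*

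**What the plan says.** The rule is in the protocol article, section Intergroup and Intragroups Analysis. It has two parts, an absolute and a relative change:

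- Absolute: "For all numeric variables percentage will be calculated with delta differences (post-test score minus the pre-test score".
- Relative, in the same sentence: "percentage’s change [(post-test score) minus (pre-test score) divided by (pre-test score) multiplied by 100". I read this as (post - pre) / pre × 100.

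The section gives both an evaluative role: "These measures will allow us to evaluate the intervention’s immediate effects and the maintenance of this effect after 4 weeks". Its dependent variables are listed as "Variables included in sleep patterns (sleep latency, sleep efficiency, sleep and waking up times, total sleep time), sleep hygiene and sleep problems". Clock times are therefore named outcomes, and nothing exempts them from the rule.

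The section on evaluating the serious game creates further numeric variables from the sticker tasks. For the bedroom task, "the total of inappropriate and suitable objects present in the bedroom will be counted". For the activity task, "The same will be for the analysis of the strategy for “mapping activities before bedtime". That section lists its own tests and does not repeat the percent-change rule.

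**The concern.** Percent change has meaning only on a scale with a true zero and a non-zero baseline. A time of day meets neither condition: its origin is a convention, and the baseline can be zero or negative under some conventions. The rule therefore assigns sleep and wake-up times a figure that cannot be read, and says that figure will help to show whether the intervention worked. Irregular sleep and wake times come first in the Introduction's hypothesis, so these outcomes matter to the trial.

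The counts are a second and weaker case. A child with no inappropriate object at baseline has a zero divisor. For small counts the measure is also asymmetric, so a group mean can suggest change where there is none.

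What is at stake is the interpretation of a reported effect summary, not the validity of the hypothesis tests.

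**Working it through.** The document gives no percent-change figure to reproduce, so the check applies its formula to cases.

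**1. Clock times.** Input: an illustrative bedtime that moves 30 minutes earlier, from 22:00 to 21:30. Formula: (post - pre) / pre × 100.

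| Time coded as | Pre (h) | Post (h) | Percent change |
|---|---|---|---|
| Hours since 00:00 | 22 | 21.5 | -0.5 / 22 = -2.3% |
| Hours since 12:00 | 10 | 9.5 | -0.5 / 10 = -5.0% |
| Hours since 18:00 | 4 | 3.5 | -0.5 / 4 = -12.5% |
| Hours relative to midnight | -2 | -2.5 | -0.5 / -2 = +25% |

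The absolute change is -0.5 h (-30 minutes) in every row. The percent change varies more than fivefold among the negative values and reverses sign in the last row. The document states no coding, so none of the four is the planned figure.

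**2. Zero baseline counts.** Input: the total of inappropriate objects or activities per child. The document gives no baseline mean, so I assume Poisson counts with means from 0.5 to 4. The share of children with no defined percent change is exp(-mean), applied here to the planned 176 children:

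| Assumed mean | Share with zero | Of 176 |
|---|---|---|
| 0.5 | 61% | about 107 |
| 1 | 37% | about 65 |
| 2 | 14% | about 24 |
| 3 | 5% | about 9 |
| 4 | 2% | about 3 |

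**3. Mean percent change when nothing changes.** By hand: if half the children go from 1 to 2 (+100%) and half from 2 to 1 (-50%), the mean percent change is (100 - 50) / 2 = +25%, while the mean difference is (1 - 1) / 2 = 0.

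By simulation: each child has a fixed underlying rate drawn from a gamma distribution (shape 4), with independent Poisson counts before and after, one million children, and no true change.

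| Assumed mean | Zero baseline | Mean difference, all children | Mean percent change, children with a non-zero baseline |
|---|---|---|---|
| 1 | 41% | 0.00 | -20.5% |
| 2 | 20% | 0.00 | +9.5% |
| 3 | 11% | 0.00 | +20.5% |

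Two effects oppose each other. Leaving out zero-baseline children removes those who could only go up, which pulls the mean down. The asymmetry of the ratio pushes it up. Which one wins depends on the baseline mean.

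**The case against.** The strongest reply is that nothing inferential rests on percent change. Groups are compared by t-test or chi-square at each of three time points, and within groups by repeated-measures ANOVA or Cochran's Q. None of these is said to use percent change, and the absolute difference is planned for the same variables in the same sentence. This stands, and it limits the point to an effect summary. It does not rescue the summary for clock times, because the section says these measures will evaluate the effect.

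Several stronger readings are tempting, and the document does not support them:

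- *Zero-baseline children are excluded from the trial's analysis.* The section Design and Procedures says "Missing data will result in individuals being excluded without outcome", but it does not say that an undefined quotient counts as missing data. Such a child has recorded values and stays in the absolute difference and in the tests.
- *The measure is biased against showing a reduction.* The simulation gives -20.5% at a mean of 1 and positive values at 2 and 3, so the direction depends on the baseline.
- *It loses the children with the best baseline.* That fits inappropriate items. Suitable objects are counted too, and there zero is the worst baseline.
- *A bedtime that crosses midnight gives absurd percentages.* Coding 00:30 as 0.5 and 23:30 as 23.5 does give (23.5 - 0.5) / 0.5 = +4600% for a bedtime one hour earlier. The same coding gives a difference of +23 h, so the fault is in the coding and would also corrupt the difference and the tests.
- *Sleep latency has the same defect.* Latency is a duration with a true zero. If the 10 nights are averaged, which the document does not state, a baseline of exactly 0 is unlikely.
- *Maintenance is not measured.* The formula names only pre-test and post-test scores, but the comparisons at three time points and the repeated-measures ANOVA also bear on maintenance.

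It is also fair to say that the counts come under the rule only through its general scope, since their own section does not repeat it.

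**Conclusion.** The point holds for sleep and wake-up times on the text alone. The rule covers every numeric variable, these outcomes are named, and percent change of a clock time has no fixed size or sign: -2.3%, -5%, -12.5% or +25% for the same 30-minute shift.

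For the object and activity counts it holds if the rule reaches them, as its wording implies. Percent change is then undefined for every child with a zero baseline count. That is between 2% and 61% of children under assumed Poisson means of 4 down to 0.5. The mean among the rest can be non-zero in either direction when the mean change is zero. These sizes rest on assumed distributions, because the document gives no baseline counts.

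A reader might infer that the trial's comparisons are compromised. They are not: the absolute difference and the planned tests keep these children and do not depend on percent change. The sample size is unaffected.

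**What to change.** Reword the percent-change sentence so that:

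- For sleep and wake-up times, percent change is dropped and the absolute difference is reported in minutes. Times are coded as minutes from a fixed evening origin, such as 18:00, so that values do not wrap at midnight.
- For the object and activity counts, percent change is dropped and the absolute difference is reported as a number of objects or activities.
- The difference is defined both as post minus pre and as follow-up minus pre, so that the summary covers the 4-week maintenance the section refers to.
- Percent change is kept only for ratio-scale outcomes with a non-zero baseline, such as total sleep time.

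The cost is one reworded paragraph and the loss of a percentage summary for these outcomes. No new data are needed, because the absolute difference is already planned and all three assessments are already scheduled.

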## Stepwise Procedures

### Participants

This study aims to recruit 176 healthy children enrolled in two private schools from Natal (Rio Grande do Norte – Brazil), as the number of children per class in these educational institutions ranges from 23 to 28. Schools will be selected by convenience, as there are difficulties to promote parental and school involvement (Jones et al., 2013; Wilson et al., 2014; Mindell et al., 2016), due to the concern of staff and parents about the activities developed in school and the necessity to adjust the research schedule to that of school activities, such as evaluation periods, vacation, science fair or school games. Furthermore, sample size was carried out using G^∗^Power 3.1.9, with alpha level of 5%, effect size of 0.5, and power of 95% for the two groups (Faul et al., 2007; Aberson, 2015). Results from this analysis indicated 88 participants to each group.

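### Within-group tests and percent changes are given the job of showing the effect and its maintenance, while the group comparisons are unadjusted for the collected baseline and none tests change

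*Protocol article*

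**What the plan says.** The protocol article, under Intergroup and Intragroups Analysis, sets out two strands.

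- **Between groups.** Sleep pattern variables, sleep hygiene and sleep problems are compared between experimental and control groups at each of the three assessments, by independent t-test or chi-square. The text says this will identify whether the game improved sleep measures and sleep hygiene.
- **Within groups.** "To evaluate possible improvements intragroup, comparisons will be conducted using: ANOVA (F) for repeated measures" with a Bonferroni post test, and Cochran's Q. The plan adds: "For all numeric variables percentage will be calculated with delta differences", together with percent change from the pre-test score. The paragraph closes by saying that these measures will evaluate the intervention's "immediate effects and the maintenance of this effect after 4 weeks".

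The section on evaluating the game repeats the split for the learning outcomes: repeated-measures ANOVA and Cochran's Q within groups, and "independent student’s *t*-test (*t*) or Chi-square test to intergroup analysis".

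The section Controlling for Covariates contains only baseline homogeneity tests. The group comparison follows once those tests show no significant difference.

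**The concern.** A change within one arm contains everything that happened between visits: the school calendar, repeated measurement, regression to the mean and any effect of the game. Removing the first three is what the control arm is for. Finding a significant change in one arm and not in the other is not a comparison of the arms. A plan that lets within-arm change speak to the effect and its maintenance leaves room for ordinary drift to be reported as efficacy.

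The between-group tests that do exist leave each child's own baseline out of the group contrast. That gives away precision, and a chance difference at baseline carries through to the later visits.

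Percent change is prescribed for every numeric variable. The listed outcomes include sleep and wake-up times, where a ratio depends on an arbitrary origin. They also include sleep latency and counts of inappropriate objects, which can be zero at baseline.

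**Working it through.** **Inputs from the article (Participants).** The sample size is given "with alpha level of 5%, effect size of 0.5, and power of 95% for the two groups", and "Results from this analysis indicated 88 participants to each group". Sidedness, the baseline–outcome correlation r and any expected drift are not given. The last two are assumed below and shown as ranges.

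**1. The plan's own figure.** Two independent means, effect size d = 0.5, power 95%, noncentral t:
- one-sided 5%: 87.26, rounded up to 88 per group, so the stated figure reproduces;
- two-sided 5%: 104.93, rounded up to 105 per group.

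The stated number is therefore that of a one-sided, unadjusted t-test at one time point. Two-sided power at 88 per group is 91.0%.

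**2. What within-group testing would show with no effect.** Suppose both arms truly change by the same amount δ, in SDs of change. A paired t-test with n = 88 stands in for the repeated-measures contrast. Its noncentrality is δ√88, its chance of significance is p, and the chance of significance in the experimental arm but not in the control arm is p(1 − p). The Bonferroni columns use 0.05/3 for three pairwise contrasts.

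| δ | p at 5% | p(1 − p) | p at 0.05/3 | p(1 − p) |
|---|---|---|---|---|
| 0.1 | 15.3% | 13.0% | 7.1% | 6.6% |
| 0.2 | 45.8% | 24.8% | 29.2% | 20.7% |
| 0.3 | 79.5% | 16.3% | 64.6% | 22.9% |
| 0.4 | 96.0% | 3.8% | 90.3% | 8.8% |

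The range is about 4–25% unadjusted and about 7–23% with Bonferroni. Since p(1 − p) cannot exceed 25%, the 0.2 row is close to the worst case at the 5% level.

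**3. Chance baseline imbalance.** The SD of the baseline difference is √(2/88) = 0.151 SD. A difference of up to 1.96 × 0.151 = 0.295 SD passes a non-significance check at 5%. An imbalance b shifts the unadjusted later difference by r × b. For b = 0.29:
- r = 0.5: shift 0.145 SD, conditional type I error 12.5%;
- r = 0.7: shift 0.203 SD, conditional type I error 19.5%.

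At a more typical imbalance of 0.15 SD the conditional error is 4.8% (r = 0.5) or 3.9% (r = 0.7), so there is no inflation. Averaged over all randomisations the unadjusted test keeps its 5%.

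**4. Gain from adjustment.** ANCOVA reduces the residual SD to √(1 − r²), so the effective size is 0.5/√(1 − r²). Two-sided power at 88 per group:
- unadjusted: 91.0%;
- r = 0.3: effective size 0.524, power 93.3%;
- r = 0.5: effective size 0.577, power 96.8%;
- r = 0.6: effective size 0.625, power 98.5%;
- r = 0.7: effective size 0.700, power 99.6%.

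None of these figures allows for clustering by class.

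**5. Percent change of a clock time.** As an illustration, a bedtime moving from 21:30 to 21:00 is (21.0 − 21.5)/21.5 = −2.3% in clock hours, but (3.0 − 3.5)/3.5 = −14.3% when hours are counted from 18:00. With a zero baseline the ratio is undefined.

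**The case against.** The plan does use its control group. The first paragraph of the same section ties improvement to the between-group tests, and those tests are run at all three visits, so maintenance also has a between-group comparison at 4 weeks. Under valid randomisation an unadjusted comparison at a later visit is a legitimate test, and adjustment is then a gain in efficiency. Baseline also enters the homogeneity tests, the repeated-measures ANOVA and the deltas. All of this stands. A reader might infer that the control group plays no part where efficacy is claimed, or that baseline is never used; the text supports neither.

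The article also never states a rule of declaring success when only the experimental arm is significant. The figures in step 2 show what such a reading would risk, not the error rate of a declared test, and they rest on an assumed drift. A single figure of 25% would be selective, because it sits at the ceiling of the formula and ignores the stated Bonferroni post test.

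Percent change is only said to be calculated, with no test attached, so that part concerns description. The closing sentence on effect and maintenance could be read as covering the whole section, but its place directly after the within-group methods and change scores favours the narrower reading.

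**Conclusion.** The point holds in a limited form. The article assigns repeated-measures ANOVA and Cochran's Q to within-group use, and says that these, with deltas and percent changes, evaluate the effect and its maintenance. It plans no between-group test of change and no baseline-adjusted group comparison. This is a stated method, not a detail left to an analysis plan.

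The existing comparisons at post-intervention and 4 weeks are valid given valid randomisation. Their weaknesses are lost precision (91.0% against 93.3–99.6% power for r from 0.3 to 0.7) and sensitivity to an unlucky baseline difference of up to about 0.30 SD. The within-group results cannot carry an efficacy claim: under equal drift in both arms, a misleading pattern in favour of the experimental arm would arise in about 4–25% of trials (about 7–23% with Bonferroni). These sizes depend on the assumed drift and correlation, on a paired t-test as stand-in, and on independent children.

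**What to change.** State that conclusions on effect and on maintenance rest on the baseline-adjusted between-group difference, with 95% CI, at post-intervention and at 4 weeks respectively.

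- **Continuous outcomes:** ANCOVA at each visit, or one linear mixed model with the two later values as response and group, time, group-by-time and baseline as fixed terms.
- **Binary outcomes:** a logistic or generalised mixed model, since a linear mixed model does not fit them.
- **Class:** account for it as the final allocation requires, because Design and Procedures describes both a coin flip by class and a random assignment of children. At 23 to 28 children per class, 176 children make about 6 to 8 classes (176/28 = 6.3; 176/23 = 7.7). A class variance would be poorly estimated from so few, and this needs care.
- **Within-group changes and deltas:** keep as description and label them so.
- **Percent change:** drop it for clock times and for variables that can be zero at baseline.

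The baseline is already collected, so no new data are needed. The cost is revised wording and slightly more analysis work, chiefly for the binary outcomes and for class.

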### Evaluation of Serious Game “Perfect Bedroom: Learn to Sleep Well”

The statistical analysis will involve analyzing the responses from the evaluation questionnaire and strategies developed by the researchers (“Set up your bedroom” and “Mapping activities before bedtime”). For the questionnaire descriptive analyze and exploration of frequency will be conducted with crosstabs command. It will allow us to characterize the children’s perception of the game in the following aspects: (a) user’s satisfaction and user’s experience; (b) understandability; and (c) enjoyment. These indicators will be collected in a typical Likert scale with a five-point ordinal scale that represents five conditions in binary data (I did not like play = 1; I did like play = 2). In addition, the software package Iramuteq will be used for the qualitative analyze of the open question “How it was to play the game Perfect Bedroom: learn to sleep well?”).

The final point of the evaluation, learning outcomes, will be evaluated with inter and intragroup analysis of the strategies cited below. The activity of mapping bedroom responses will be categorized in binary data (object absent in bedroom = 1; object present in bedroom = 2) and the total of inappropriate and suitable objects present in the bedroom will be counted. Attribution in each group will occur according to previous studies indicating the negative effect of electronic devices in children’s room (Cain and Gradisar, 2010; Cespedes et al., 2014). The same will be for the analysis of the strategy for “mapping activities before bedtime.”

Inferential tests to intragroup and intergroup will be carried out in binary and numeric data, respectively, ANOVA (F) for repeated measures with Bonferroni’s post test and Q Chochran test to intragroup; and independent student’s *t*-test (*t*) or Chi-square test to intergroup analysis.

